# Intervention With WhatsApp Messaging to Compare the Effect of Self-Designed Messages and Standardized Messages in Adherence to Antiretroviral Treatment in Young People Living With HIV in a Hospital in Lima, Peru: Protocol for a Nonblinded Randomized Controlled Trial

**DOI:** 10.2196/66941

**Published:** 2025-05-22

**Keywords:** mHealth, HIV, WhatsApp, adherence, ART, people living with HIV, young people, mobile phone messaging, digital app, messaging intervention, antiretroviral treatment, behavioral change technique, design, evaluation, self-design, randomized controlled trial, Peru

## Abstract

**Background:**

Young people living with HIV face challenges in consistently adhering to antiretroviral therapy (ART). Although mobile health interventions, particularly those using SMS text messaging, have been implemented to improve ART adherence, many lack a focus on specific behavioral mechanisms. Interventions incorporating behavioral change techniques (BCTs), especially those emphasizing customization, may enhance effectiveness. WhatsApp offers potential for delivering tailored, behaviorally grounded interventions with diverse communication features. We hypothesize that WhatsApp messages self-designed by participants, with spontaneous targeting of BCTs, could be more effective than standard WhatsApp messages designed by the researchers to improve ART adherence.

**Objective:**

The objective of this study is to evaluate the effectiveness of WhatsApp messages created by participants (self-designed) compared to WhatsApp messages designed by the researchers (standardized) over adherence to ART at 16 weeks of intervention in young people living with HIV who receive HIV care under routine conditions at a public hospital in Lima, Peru.

**Methods:**

A 2-arm randomized controlled trial with a parallel assignment of 1:1, with no blinding of study intervention, was performed. Eligible participants are consenting people living with HIV aged 18-29 years who receive HIV care at the study center and whose mobile phones support WhatsApp. Following informed consent and a baseline survey on clinical and personal preferences (eg, timing and frequency of messages), participants are randomized to the control group (messages designed by the research team) or to the experimental group (messages designed by participants), stratified by sex, educational level, current ART intake, and history of ART abandonment. Participants in both groups receive up to 3 WhatsApp messages per week for 16 weeks. ART adherence, the primary outcome, is measured using the Simplified Medication Adherence Questionnaire (SMAQ) at 4, 8, 12, and 16 weeks. Monthly feedback questionnaires on user experience are also administered. The WhatsApp chat format allows two-way communication between participants and the research team throughout the study. We will compare ART adherence between 2 groups at 16 weeks under the intention-to-treat principle, with no interim analysis planned. Based on an estimated 10% difference in adherence, 78.9% power, and a 2-sided α of .05, the target sample size was set at 120, later increased to 131 to include a 2-week pilot phase.

**Results:**

In March 2024, we started enrolling and randomizing participants. The study follow-up will continue until the last participant completes 16 weeks of intervention (November 2024). As of February 2025, we are in the process of data curation.

**Conclusions:**

This trial will compare the effectiveness of standardized vs self-designed WhatsApp messages on ART adherence measured at 16 weeks among young people living with HIV receiving routine care in a low-resource setting in Lima.

**Trial Registration:**

ClinicalTrials.gov NCT06500013; https://clinicaltrials.gov/ct2/show/NCT06500013

**International Registered Report Identifier (IRRID):**

DERR1-10.2196/66941

## Introduction

HIV programs continue in search of effective interventions to increase adherence to antiretroviral therapy (ART), especially for young people living with HIV/AIDS. This group faces increasing rates of new HIV infections [1] and heightened vulnerability to drivers of antiretroviral resistance, such as suboptimal ART adherence [2], ART abandonment, and non-retention in care [3].

Mobile health (mHealth) interventions tailored to young people living with HIV/AIDS seem highly promising, considering that so-called Gen Z tend to be digital natives who routinely use apps. At first glance, messaging interventions to improve adherence seem practical, low-cost, and prone to tailoring to users’ needs [4,5]. However, medication adherence involves complex behavioral aspects. Several behavioral change theories, notably the transtheoretical model, have been applied in interventions to improve medication adherence [6-8], often with contradictory findings [9,10]. The heterogeneity of findings may respond to messaging interventions operating simultaneously over different behavioral aspects, for instance, reminders and motivation. While a weekly frequency of delivery and a bidirectional platform have proven effective [11], the message’s content seems crucial to achieving behavioral changes [12].

Due to difficulties in identifying the specific factors responsible for behavioral changes, Abraham and Michie [13] developed a standardized system to isolate the drivers of behavior change: behavioral change techniques (BCTs). Since then, several interventions have adopted the BCT taxonomy to more accurately target specific behavioral aspects, improve the rigor and replication of behavioral studies, and enhance their reliability [14,15].

Most messaging interventions to improve adherence to ART have involved SMS and worked with standardized messages created by researchers. Currently, young people in low- and middle-income countries, including people living with HIV/AIDS, extensively use WhatsApp [16-18]. This app's multiple content and delivery options facilitate integrating BCTs into message design. Moreover, WhatsApp allows documentation of intervention delivery processes, including records of scheduled, sent, read, and answered messages.

As self-designed products can convey more significance to users [19] based on an increased sensation of authenticity and usefulness [20], in this study, we implement an intervention to support ART adherence through WhatsApp messages with self-designed messages in one group and standardized messages in the second group under the hypothesis of more effectiveness for the group of self-design.

For the main analysis, we will compare the efficacy of both types of messages using the Simplified Medication Adherence Questionnaire (SMAQ), a validated ART adherence questionnaire measured at 16 weeks of intervention. As the use of mHealth is incipient in our setting, the study protocol includes secondary mixed-methods components aimed at understanding the acceptability of the intervention and the challenges participants face throughout its delivery.

## Methods

### Setting

In 2023, overall, 87.1%-90% of Peruvian people between 18 and 29 years of age had access to a mobile phone, with growing trends among lower socioeconomic groups [21]. The per capita country's GDP stood at US $7789.9 [22].

This study is conducted at Hospital Nacional Cayetano Heredia in Lima, Peru’s largest city and home to over 60% of people living with HIV in Peru [23]. As part of the network of health services provided by the Peruvian Ministry of Health, this hospital serves primarily people from low-resource backgrounds and provides outpatient and inpatient HIV services to over 5000 people living with HIV. Conditioned on stocks, ART is usually dispensed monthly by HIV program nurses as walk-ins on a first-come, first-served basis at the offices of the HIV program. Pregnant people living with HIV have a much closer medical follow-up than the rest of the patient population (outside children), with monthly appointments with doctors, additional counseling services at their primary care clinics, greater priority for viral load and CD4 lymphocyte testing, and regular appointments with midwives in which adherence to ART is reinforced.

Through a longstanding alliance with Instituto de Medicina Tropical Alexander von Humboldt from Universidad Peruana Cayetano Heredia, this hospital's HIV Program continuously promotes clinical and operational research.

### Study Design

A randomized controlled trial with 2 arms and a 1:1 assignment ratio will be conducted.

### Eligibility Criteria

We assessed the eligibility criteria at the first encounter with potential participants, as follows (Textbox 1).

We excluded pregnant people since their level of care differs significantly from the rest of our potential study population, which would introduce bias regarding the effects of receiving the intervention on ART adherence.

Inclusion and exclusion criteria.
**Inclusion criteria**
People living with HIV receiving HIV care at the study centerPeople living with HIV aged 18-29 yearsOwnership of a mobile phone that supports WhatsApp
**Exclusion criteria**
PregnancyImpossibility to read WhatsApp messages due to illiteracy or blindness

### Study Procedures—Preimplementation Phase

First, during the study's design, we consulted with health staff to better respond to the study’s population needs without disrupting routine HIV program operations. Once the study design was completed, the coordination was intended to communicate study standard procedures and facilitate the study's implementation. Our institutional review board (IRB) approved the full study protocol in July 2023. Then, we designed the web-based study platform with Infobox Latinoamérica, a Peruvian IT company. The web-based study platform is integrated with WhatsApp business and supports the delivery of personalized and standardized messages, a Chatbot for mass-sending questionnaires and continuous chat with participants. The Infobox provides technical support during the study as required.

The principal investigator (PI) completed the web-based training on BCT-Taxonomy to design the standardized messages. He created 44 standardized messages, each corresponding to one of 14 selected BCT categories, though the final format considered elements of other behavior change theories (health belief model, social support theory, and social cognitive theory). The number of standardized messages minimized the chance of participants receiving repeated messages during the study period. Table S1 in Multimedia Appendix 1 lists all standardized messages with their corresponding BCTs in the order those messages are sent to participants.

We created the randomization sequence using the REDCap (Research Electronic Data Capture) randomization module (REDCap Consortium); sex assigned at birth, educational level, current ART intake, and previous ART abandonment were the criteria for stratified randomization.

### Study Procedures—Implementation Phase

To preserve confidentiality, nurses from the HIV Program are informed about the study’s eligibility criteria and collaborate to identify potential participants. While they wait for infectious diseases outpatient consults or ART pick-ups, the nurses inform them about the study. For those interested, we reassess eligibility, explain the study in detail, and obtain informed consent privately (a model of our consent form is shown in Multimedia Appendix 2). Then, we fill out a REDCap baseline questionnaire, collect data to send messages through the study web-based platform, and, when applicable, explain and support the process of self-designing the messages. Figure 1 presents participant identification, recruitment, and allocation. After completing the baseline questionnaire, which provides information for stratification (sex assigned at birth, educational level, current ART intake, and previous ART abandonment), participants are randomized to one of 2 study arms allocated with a 1:1 proportion. Then, the research staff informs participants of their assigned group and provides details accordingly. Given the characteristics of the intervention, neither the researchers nor the participants are blinded.

Participants allocated to the self-designed messages group draft 10-15 messages that would help them take their ART; this number assures similitude in the number of messages received per participant in both study arms. Message creation is done during enrollment. Participants determine the final content of their messages. However, during their creation, the research staff ensures that the content excludes potentially harmful or offensive topics. If there are any doubts during the process, the staff provides support by offering examples based on characteristics identified during the baseline questionnaires and general conversation with participants (such as family, personal hobbies, goals, and other general topics). After the messages are created, the data manager reviews them and may slightly modify them to ensure clarity while keeping the original content. Once the messages are ready, the data manager enters them into the study messaging platform.

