### Data Collection

For this study, data collection and management use REDCap electronic data capture tools hosted at Universidad Peruana Cayetano Heredia [24]. The enrollment form collects participants’ baseline sociodemographic data, history of ART, strategies for taking ART, assessment of their adherence with the SMAQ, depression screening, stigma, an evaluation of their satisfaction with the health services provided at the study center, and a measurement of their knowledge about ART and adherence. For participants allocated to the self-designed messages arm, we also register their created messages in REDCap. In total, 4 members of the research team are involved in data collection. The PI trained them with mock interviews and a web-based course on using REDCap.

We used an intermediate Excel file hosted in a secured drive to schedule messaging and questionnaire delivery per participant through the web-based study platform. This file contains the identification codes, a list of messages, and the date and time of sending.

The web-based study platform collects CSV file data on every message and questionnaire scheduled, sent, received, read, and answered per participant and chat sessions with providers. The records include anonymous hour-dated logs of all conversation contents with participants, including reasons for adding, modifying, or eliminating messages in the self-designed group and responses to study questionnaires.

To obtain the total number of eligible patients who meet eligibility criteria, independent of whether they are invited to participate, we collect routine data from the study center regarding the number of outpatient consults and patients in the age group of interest who pick up ART during the study period.

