### Data Management

All study data are stored in secure, password-protected platforms, with access restricted to the authors of this protocol. Members of the research staff review data collected at baseline to ensure accuracy and completeness. Weekly, we download CSV files and reports from the web-based study platform. To ensure the records' accuracy, we compare a subset with the corresponding intermediate Excel file containing messages and questionnaires scheduled for delivery. Data curation will be performed at the end of the trial to point out missing values, identify any measurement outside the expected range, and evaluate strategies for mitigating these occurrences.

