Additionally, we will perform a descriptive analysis of participants’ baseline characteristics overall and by study groups. We will also report the percentage of participants adherent to ART per study group at 4, 8, and 12 weeks of intervention. We will describe the characteristics of the intervention delivery, including the frequencies and percentages of messages received, read, and answered by participants. We will conduct all these analyses, blinding the study groups.

We will perform a thematic analysis of the most common themes in self-designed messages to evaluate relevant qualitative outcomes. In addition, we will report the median number of messages created by participants and the main reasons for adding, modifying, or eliminating messages.

We will report the results following the CONSORT-EHEALTH (Consolidated Standards of Reporting Trials of Electronic and Mobile Health Applications and Online Telehealth) statement for randomized controlled trials [25].

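### The promised blinding of the analyses is not assured: researchers are unblinded, the records reveal the arm, and curation and covariate choice have no stated protection

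*Protocol article*

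**What the plan says.** All references are to the protocol article.

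- **Abstract, Methods:** the trial is described as two-arm, "with no blinding of study intervention, was performed".
- **Study Procedures—Implementation Phase:** "Given the characteristics of the intervention, neither the researchers nor the participants are blinded". Research staff tell participants their group and support the drafting of messages. The data manager edits, enters and schedules messages. The chat physicians, and where needed the principal investigator, review later changes to self-designed messages.
- **Data Collection:** "For participants allocated to the self-designed messages arm, we also register their created messages in REDCap". The scheduling file links identification codes to each participant's messages. The platform records hold conversation content, including reasons for changing "messages in the self-designed group and responses to study questionnaires".
- **Data Management:** "All study data are stored in secure, password-protected platforms, with access restricted to the authors of this protocol". Also: "Weekly, we download CSV files and reports from the web-based study platform". A subset of the downloads is checked against the scheduling file. At the end of the trial, curation identifies missing and out-of-range values and considers how to deal with them.
- **Data Analysis Plan:** the logistic model is built stepwise. Study group is always in it, and other variables stay or go according to how the odds ratios and standard errors change. After a paragraph of descriptive analyses comes the sentence: "We will conduct all these analyses, blinding the study groups".
- **Results:** curation was in progress in February 2025.

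**The concern.** The article makes a positive claim of blinded analysis, but the people, access rights and files it describes do not deliver one. Everyone whose hands-on role is described knows or can see the arm, and no masked analyst or coded analysis file is mentioned. Relabelling the arms A and B does not hide them from someone who also holds the message files.

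This matters because two later steps need judgement: how to treat missing or out-of-range values, and which covariates to keep. The outcome is a self-reported yes/no result, with few non-adherent participants expected. If these choices are made by people who know the arm, or who watch the treatment odds ratio move, they can tilt the result without anyone intending it. A reader of the final report would meanwhile take the analysis as masked.

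**Working it through.** The plan gives no figure for blinding, so there is none to reproduce. The check compares statements. A short calculation then shows how sensitive the primary comparison is.

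**1. Who could be blind?** Researchers are unblinded (Implementation Phase), and data access is limited to the authors (Data Management). The article identifies no author who is kept apart from enrolment, message entry or chat. A masked author-analyst is possible but not described.

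**2. Do the records reveal the arm?** REDCap has a created-messages entry for one arm only. The scheduling file lists messages by identification code, and the standardized messages are a fixed set of 44 in a fixed order (Preimplementation Phase). Anyone with either source can therefore tell the arm. The second source is an inference, though a strong one. Counts of messages received, read or answered need not reveal it: both arms get up to 3 messages a week, and the number of drafted messages is meant to keep the arms similar.

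**3. What does the blinding sentence cover?**
- Narrow reading: only the descriptive paragraph it closes. The primary model then carries no blinding claim and no protection.
- Broad reading: the models too. Coded labels would then hide which arm is which only from someone without the message files. Even for that person, the study-group odds ratio is visible at each selection step, because study group is forced into the model.

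On neither reading does the sentence mention curation.

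**4. How fragile is the primary comparison?** Inputs: 90% versus 80% adherent, 120 participants, raised to 131 (Sample Size Determination). The 65/66 split of 131 is my assumption. With adherent and non-adherent counts a, b in one arm and c, d in the other, the Pearson statistic is X² = N(ad − bc)² / (product of the four margins). The continuity-corrected version replaces |ad − bc| by |ad − bc| − N/2.

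Expected non-adherent at 60 per arm: 6 + 12 = 18.

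- 54/60 v 48/60: X² = 120 × 360² / (60 × 60 × 102 × 18) = 2.353
- 55/60 v 47/60: X² = 120 × 480² / (60 × 60 × 102 × 18) = 4.183; corrected, 120 × 420² / (60 × 60 × 102 × 18) = 3.203
- 59/65 v 53/66: X² = 131 × 449² / (65 × 66 × 112 × 19) = 2.893
- 60/65 v 53/66: X² = 131 × 515² / (65 × 66 × 113 × 18) = 3.982; corrected, 131 × 449.5² / (65 × 66 × 113 × 18) = 3.033

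| Adherent | p, uncorrected | p, corrected |
|---|---|---|
| 54/60 v 48/60 | 0.125 | 0.20 |
| 55/60 v 47/60 | 0.041 | 0.074 |
| 59/65 v 53/66 | 0.089 | 0.146 |
| 60/65 v 53/66 | 0.046 | 0.082 |

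At 60 per arm, a single changed record does not reach 0.05 even uncorrected: 55/60 v 48/60 gives 0.067 and 54/60 v 47/60 gives 0.080. The plan says only chi-square and does not state whether a correction is used.

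**The case against.** The strongest reply is that nothing here is contradictory. The article ties the lack of blinding to the nature of the intervention, and an open-label trial can still be analysed with coded arms. One of the authors may be a separate analyst, and the handling of the key may be set out in a full protocol or analysis plan that is not shown. This stands. It is why the point is that blinding is not assured, and not that it is absent.

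Several stronger readings are tempting, and the documents do not support them.

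- **That curation and model choices are known to be unblinded.** The text does not say so. For curation, the article makes no promise of blinding, so the safeguard is unstated and not contradicted.
- **That the weekly downloads amount to looking at outcomes.** They are described alongside record-accuracy checks, the adherence questionnaire goes out only every 4 weeks, and preliminary outcome analyses are ruled out.
- **That the delivery tabulations give away the arm.** Counts need not; message text would.
- **That a few curation decisions would decide significance.** The p-value examples change valid yes/no answers, whereas the described curation concerns missing and out-of-range values. No example is below 0.05 with continuity correction, and the number of disputable records is unknown.

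It can also be said that stepwise selection is a separate problem from blinding. That is fair, but here the two meet: the selection rule itself exposes the treatment estimate while covariates are being chosen.

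**Conclusion.** The point holds in a limited form. The article claims blinded analyses, but its own account of roles, access and records does not secure them, and the reach of the claim over the primary model is unclear. The two discretionary steps, missing-value strategy and covariate retention, have no stated protection. That goes beyond missing detail, because the covariate rule as written has the analyst watching odds ratios in a model that already contains the arm.

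No size of bias can be given, and the documents do not show that any occurred. The calculation shows only that the comparison rests on about 18 non-adherent participants at the design rates and is sensitive to a few records and to the choice of test. The conclusion assumes that no masked analyst or stripped file is set out in a document not shown. If one is, the remaining task is to state it in the article and bring the covariate rule into line.

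**What to change.** 1. The data manager exports a file with a participant key, baseline variables, SMAQ results, ART pick-up visits, and loss-to-follow-up and permanence times derived from response and read timestamps. It leaves out the arm, message text, created-message fields and chat logs. Pick-up visits and permanence must be included because the current model requires them.
2. Curation, missing-data rules and the covariate list are decided and signed off on that file. Covariates are chosen on prognostic grounds and not on changes in the study-group odds ratio. The Data Analysis Plan is amended to match, since its present rule cannot be followed without the arm.
3. The arm is then merged, and the primary, repeated-measures and survival analyses are run as fixed.
4. The blinding sentence is reworded to say which analyses and which people are blinded. No blinding is claimed for analyses of message content. Any curation or model decisions already made by people who knew the arm are reported as unblinded; this is relevant because curation was in progress in February 2025.

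The cost is one restricted export by the existing data manager and some rewording. The downside is that covariate choices can no longer be revised once the arm is seen.
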